7.6.3 Sample size considerations

7.6.3.1 Primary outcome

The sample size of the present study is based on the following event rates: the 3 year all cause mortality rate among subjects with ESRD is 44% based on RENINE data. CV mortality constitutes 40-60% of the total group of deaths, leading to a 3 year CV mortality rate of 22% in HD patients. Assuming that the incidence of non-fatal CVD is equal to the CV mortality rate (22%), we assume a three year incidence of fatal and non-fatal CVD of 44%. In addition, based on experience around 8% of the ESRD patient will undergo renal transplantation yearly and as such is being censored in the trial.

Assuming that HDF will reduce all cause mortality with 20%, we estimate that with a two-sided alpha of 0.05 and a power of 80%, about 772 patients need to be enrolled and followed for three years. In these patients we expect about 250 events to come to a decision.

Assuming that HDF will also reduce the incidence of fatal and non-fatal CVD with 20%, we estimate that with a two-sided alpha of 0.05 and a power of 80%, the same amount of patients need to be enrolled and followed for three years. (Note that the total number of patients to be included can not be specified in advance because of the planned sequential [interim] analyses.)

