# 7.1.2 Participating centers

All dialysis centres which are able to perform on-line hemodiafiltration in the Netherlands will be asked to participate in the study to obtain a total patient number of 772.As of yet, 17 centres have agreed to participate in the study. Participating centres should include a minimum of 10 patients.

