7.6.4 Interim analysis

In this study, sequential (interim) analyses will be performed. The reason for this approach is that on average less patients are needed in the study when the expected difference in the primary outcome variable is real or when no difference can be expected anymore. Sequential analyses are performed on survival outcome variables according to the double triangular test as described by Whitehead[[117]](#endnote-118) and implemented in the computer programme PEST version 4.[[118]](#endnote-119) The sequential (interim) analyses will be performed by an independent data monitoring board (DMB).

This DMB will be initiated to evaluate the findings of the interim analyses. The DMB consists of a biostatistician (chairman), a nephrologist, an internist, a vascular surgeon and a clinical epidemiologist. The steering committee will provide the DMB every 2 months with the relevant database to perform the unblinded analyses. The main task of the DMB is to decide whether the analyses provide definite proof of either efficacy or no efficacy with respect to the primary outcome. The limits upon which these decisions are to be decided have been defined at the start of the study by the steering committee, advised by the biostatistician [name].

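### 772 patients followed for three years are presented as the number needed for 80% power, but that size does not secure it; the 80% depends on a sequential maximum of about 580 events that the protocol does not state

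*Protocol*

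**What the plan says.** Section 7.6.3.1 gives its inputs for all-cause mortality as follows: "the 3 year all cause mortality rate among subjects with ESRD is 44% based on RENINE data"; "around 8% of the ESRD patient will undergo renal transplantation yearly and as such is being censored in the trial"; and an effect worded as "Assuming that HDF will reduce all cause mortality with 20" percent, without saying whether this is a reduction in three-year risk or in hazard. At two-sided 5% and 80% power it concludes that "about 772 patients need to be enrolled and followed for three years. In these patients we expect about 250 events" for a decision. It claims the same size for fatal and non-fatal cardiovascular events, also from 44% and a 20% reduction. It then adds in brackets: "Note that the total number of patients to be included can not be specified in advance because of the planned sequential [interim] analyses".

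Elsewhere the number takes different roles. The Summary calls 772 expected. Section 7.1.2 approaches centres "to obtain a total patient number of 772". Section 7.2.2 sets three years of allocated treatment, and the flow chart in section 4 ends at month 36.

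Section 7.6.4 fixes the monitoring method: "Sequential analyses are performed on survival outcome variables according to the double triangular test", with data going to the monitoring board every two months. It justifies the method as needing fewer patients on average. The protocol gives no maximum number of events or patients, and no rule for what happens if 772 patients complete three years without a boundary being crossed.

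**The concern.** The sentence in 7.6.3.1 ties a number of patients and a length of follow-up to a power, using the language of a requirement. Its inputs do not give that power at that size. The figure of 250 events looks like an average from the sequential test, and an average is not enough to guarantee power: a sequential test keeps its power only if the trials that run longer than average are allowed to do so.

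The practical risk is that 772 patients for 36 months becomes the actual end of the trial. A true effect of the planned size would then be missed about one time in three, and a null result on a primary endpoint would be read as coming from a trial with 80% power.

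**Working it through.** **Inputs.** From 7.6.3.1: control three-year mortality 44%, reduction 20%, transplantation 8% per year (censored), two-sided alpha 0.05, power 80%. From 7.2.2: 1:1 allocation (386 per arm) and three years. My assumptions: constant hazards, full three-year follow-up, no other loss.

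**1. Effect.** Read as a risk reduction, 44% falls to 0.80 × 44% = 35.2%. HR = ln(0.648)/ln(0.56) = 0.748, and ln HR = −0.290.

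**2. Trying to reproduce 772 as a fixed-sample requirement.**
- Events = 4(1.960 + 0.842)² / 0.290² ≈ 373.
- Yearly hazards: control −ln(0.56)/3 = 0.193; HDF −ln(0.648)/3 = 0.145; transplant −ln(0.92) = 0.083.
- Probability of an observed death by three years = λ/(λ+μ) × [1 − exp(−3(λ+μ))]: control 0.394, HDF 0.314, mean 0.354.
- Patients = 373/0.354 ≈ 1,054. Without transplant censoring, fixed-sample formulas give about 944 to 967.

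So 772 does not reproduce at two-sided 5%. A one-sided 5% test without transplant censoring comes close (755 to 762 patients), but that contradicts the stated alpha and the stated censoring, and implies about 300 events.

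**3. What 772 patients for three years supply.** Expected deaths = 386 × (0.394 + 0.314) ≈ 273. Without transplant censoring: 386 × (0.44 + 0.352) ≈ 306.

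Power = Φ(½√D × |ln HR| − 1.96):

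| Reading | Deaths D | Power |
|---|---|---|
| HR 0.748, transplant censoring | 273 | 67% |
| HR 0.748, no transplant censoring | 306 | 72% |
| HR 0.748, exactly 250 events | 250 | 63% |
| HR 0.80, transplant censoring | 280 | 46% |

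No reading reaches 80%.

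**4. The double triangular test.** With 0.025 in each tail and 80% power, the working effect is 2 × 1.960 × 0.290/(1.960 + 0.842) = 0.406. The triangle has a = (2/0.406) × ln(1/0.05) ≈ 14.77 and c = 0.406/4 ≈ 0.1014. Its boundaries meet at information a/c ≈ 145.6, which is 4 × 145.6 ≈ 582 events.

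Simulation (100,000 runs, correction for discrete looks, looks about every 3 to 15 events) gives, under the planned effect:
- power 80%, with a two-sided type I error of 5% under no effect;
- mean stopping point 253 to 257 events (261 with only 18 looks), median about 240 to 250, 90th percentile about 390;
- 39% to 42% of trials undecided at about 273 deaths, with about 50% to 53% having crossed for efficacy by then.

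The figure of about 250 therefore does reproduce, as the average stopping point at HR 0.748. At HR 0.80 the average would be about 430 and the maximum about 983, so the 250 points to the risk-reduction reading.

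If the trial were cut off at about 273 deaths, a final test that preserves alpha would bring power to about 66%; it cannot exceed the fixed-sample 67%.

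**5. From events to patients.** At 0.354 deaths per patient over three years, 250 events correspond to about 706 patients and the maximum of 582 to about 1,640. How 772 was obtained from 250 is not documented.

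**The case against.** The strongest reply is that the planned design is not a fixed one. Section 7.6.4 specifies the double triangular test, the note in 7.6.3.1 leaves the total open, and the Summary calls 772 expected. On that design the stated 80% at two-sided 5% reproduces. Comparisons with 373 events or 1,054 patients concern a design that was not chosen. The wording in 7.1.2 is a reason for approaching centres, not a closing rule. The maximum is also an extreme, since nine trials in ten would stop by about 390 events under the planned effect. Section 7.6.4 says that decision limits were set at the start, and their detail may sit in a statistical analysis plan.

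Most of this stands, and it rules out two stronger readings. A reader might infer that the trial as designed has only 66% to 67% power. The protocol does not support that, because it states no cap at 772 patients for 36 months and its own note speaks against one. A reader might also infer that the protocol gives 250 as the number of events required. It does not: it gives 250 as an expectation.

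What the reply does not rescue is the sentence linking 772 patients and three years to 80% power. It is worded as a need, it conflicts with the note in the same section, and the recruitment target, treatment period and flow chart all follow it. The exact boundaries may be left to an analysis plan, but here the protocol states the size and its justification, and states them wrongly.

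**Conclusion.** The point holds in this form: 772 patients followed for three years do not secure 80% power at two-sided 5%, although 7.6.3.1 says they are needed for it. That size supplies about 273 deaths. If it were the limit, power would be about 67% at HR 0.748, or 46% if the 20% is a hazard reduction. The planned sequential test has 80% power only if it may run to a maximum of about 580 events, and about 40% of trials under the planned effect would need more events than 772 patients for three years provide.

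The 67% is conditional on closure at that size and is not the power of the open-ended design. The results rest on constant hazards, complete three-year follow-up and no loss other than transplantation. Further loss would lower the number of deaths. The fixed-sample conclusion does not depend on the transplant assumption, since dropping it still leaves 72%.

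**What to change.** Restate 7.6.3.1, with matching wording in the Summary and 7.1.2:
- Label 250 as the expected number of events at stopping and 772 as the expected enrolment, not the number needed for 80% power.
- State the maximum number of events on which the 80% depends (about 580 under the risk-reduction reading), and that power is only about 67% if the trial closes at 772 patients for three years.
- Say whether the 20% is a risk or a hazard reduction, for both primary endpoints.
- State that event follow-up of all randomised patients, or recruitment, continues until a boundary is crossed or a common closing date is reached, rather than ending for each patient at 36 months. This concerns the recording of events, not the duration of allocated treatment.

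The cost is protocol wording, a less favourable stated power, and some extra record review if event follow-up runs beyond 36 months.

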7.6.3.2 Secondary outcomes

The sample size consideration with respect to measures of vascular damage (atherosclerosis) are based a number of issues:

- The estimated progression rate in HD patients

- The estimated standard deviation of the individual progression rates

- The effect the treatment would have on the progression rates.

For CIMT and PWV these estimates are not available for HD patients, so we have to rely on data from other patients, e.g. patients with coronary heart disease.

For common CIMT among subjects with hyperlipidemia or hypertension or subjects with previous CV disease a median annual progression rate in CIMT of 0.021 mm/yr was found in the placebo groups of randomised controlled trials. Because CIMT progression rates for HD patients are lacking, data on the standard deviation of the CIMT progression estimate for an individual is also lacking. From the overview of placebo groups of several randomised controlled trials, a median standard deviation for the common CIMT was found of 0.053 mm/yr. With these estimates, we are able to detect a treatment effect of 80%, with a power of 80% and a two-sided alpha of 5% using 155 patients per treatment arm.

The above mentioned data for PWV are even more limited than that for CIMT. Based on cross-sectional data among healthy men aged 40-80 years, an increase in PWV per year is around 0.42 m/s. The standard deviation of repeated PWV measurements, as an estimate of the progression rate, is 1.0 m/s. With these estimates, we are able to detect a treatment effect of 80%, with a power of 80% and a two-sided alpha of 5% using 138 patients per treatment arm.

The above mentioned data for LVMi are even more limited than for PWV and CIMT. Based on two observational studies among patients who were on dialysis, 54,[[116]](#endnote-117) the estimated mean change in LVMi, assessed using 2D echocardiography in a 3 year period is around 10 g/m2 with an estimated SD of 47. With a sample size of 155 subjects per treatment arm as needed for CIMT measurements, we will be able to detect a treatment effect of 150% with a power of 80% and a two-sided alpha of 5%.

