7.5.5 Vessel wall measurements

With respect to carotid intima-media thickness (CIMT), the outcome is the change in mean common CIMT, defined as the average of the intima-media thickness measurements performed circumferentially at pre-defined angles for the near and far wall of 10 mm segments of the right and left distal common carotid arteries, the far wall of the bifurcation and the far wall of the internal carotid artery. A limited number of centers is going to be involved in the CIMT measurements in this study. Centers will be trained according to a central uniform carotid ultrasound protocol. Before actually starting the study, sonographers need to be certified as outlined in the CIMT ultrasound protocol. Measurements will be performed at baseline and then annually on a midweek non-dialysis day.The ultrasound scan is being recorded on videotape and analyzed off line by a core laboratory. QA/QC procedures as existing and applied in several (inter)national trials will implemented.

Pulse wave velocity (PWV) is determined to provide additional information on functional changes of the arterial wall. The outcome measurement is the change in aortic PWV. A limited number of centers is involved in the PWV measurements in this study. Centers will be trained according to a central uniform PWV protocol. Before actually starting the study, technicians need to be certified as outlined in the protocol. Measurement data are checked regularly on quality control aspects as defined in the protocol (see appendix). Measurements will be performed at baseline and then annually on a midweek non-dialysis day.

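### The CIMT, PWV and LVMi sample sizes in 7.6.3.2 make no allowance for the deaths and transplantations that 7.6.3.1 assumes, so the stated 80% power holds only for completely followed patients

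*Protocol*

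**What the plan says.** Section 7.6.3.2 sizes three secondary outcomes, each from a mean change and an SD.

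- **CIMT:** "a median annual progression rate in CIMT of 0.021 mm/yr was found" in placebo groups, and "a median standard deviation for the common CIMT was found of 0.053 mm/yr". The claim is an 80% effect "with a power of 80% and a two-sided alpha of 5% using 155 patients per treatment arm".
- **PWV:** "an increase in PWV per year is around 0.42 m/s". The SD is 1.0 m/s, described as coming from repeated measurements and used for the progression rate. The claim is an 80% effect with 138 per arm.
- **LVMi:** a three-year change of 10 g/m2 with SD 47. With the 155 per arm taken over from CIMT, "we will be able to detect a treatment effect of 150% with a power of 80" per cent.

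The section mentions no loss to death, transplantation or withdrawal, and does not say whether the numbers are enrolled or evaluable patients.

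Section 7.6.3.1, directly before it, assumes that "the 3 year all cause mortality rate among subjects with ESRD is 44% based on RENINE data", that HDF lowers this by 20%, and that about 8% a year are transplanted and censored.

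Section 7.6.2 plans a linear random-coefficient model for CIMT and a similar approach for PWV and LVM. Section 7.5.5 limits CIMT and PWV to some centres. Section 7.5.4 sets no such limit for LVMi.

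Section 7.5.5 names the CIMT outcome after the common carotid but averages in "the far wall of the bifurcation and the far wall of the internal carotid artery".

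**The concern.** Two adjacent subsections rest on different populations: one loses more than half of the control arm over three years, the other loses nobody. Hypothesis 3 and three secondary objectives depend on these measurements. A reader who takes 80% power at face value would read too much into a null result.

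Two inputs also fit poorly with what will be analysed. The CIMT mean and SD are for the common carotid, whereas the defined outcome includes other segments. The PWV SD may be a measurement SD in m/s rather than the SD of a yearly slope.

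**Working it through.** **1. Reproduce the plan's figures.** With n per arm = 2 × (SD/δ)² × (1.96 + 0.842)² and (1.96 + 0.842)² = 7.85:

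| Outcome | δ | SD | n, no loss | Stated |
|---|---|---|---|---|
| CIMT | 0.8 × 0.021 = 0.0168 mm/yr | 0.053 | 156.2 | 155 |
| PWV | 0.8 × 0.42 = 0.336 m/s/yr | 1.0 | 139.0 | 138 |
| LVMi | 1.5 × 10 = 15 g/m2 | 47 | 154.1 | 155 |

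The match leaves no room for attrition.

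**2. Retention from 7.6.3.1.** Constant hazards are assumed. HDF mortality is 0.8 × 44% = 35.2%. The proportion alive and untransplanted at year t is 0.56^(t/3) × 0.92^t for HD and 0.648^(t/3) × 0.92^t for HDF.

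| Year | HD | HDF |
|---|---|---|
| 1 | 75.8% | 79.6% |
| 2 | 57.5% | 63.4% |
| 3 | 43.6% | 50.5% |

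Of 155 enrolled per arm, about 68 and 78 reach the 36-month visit.

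**3. Power under the planned model.** Patients with partial follow-up contribute, but with less precise slopes. The variance of one patient's slope is τ² + σ²/Sxx, where τ² is the between-patient part, σ² the visit error, and Sxx = 0.5, 2 and 5 for annual visits ending at year 1, 2 and 3. The total is set so that a full three-year series has the stated SD. The protocol does not give the split between τ² and σ², so both extremes are shown.

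CIMT, all visit error: relative information per patient is 0.1, 0.4 and 1.
- HD: 0.183 × 0.1 + 0.139 × 0.4 + 0.436 = 0.510, or 79.0 effective patients of 155.
- HDF: 0.162 × 0.1 + 0.129 × 0.4 + 0.505 = 0.572, or 88.7.
- SE = 0.053 × √(1/79.0 + 1/88.7) = 0.00820. Power = Φ(0.0168/0.00820 − 1.96) = 54%.
- Detectable slope difference = 2.80 × 0.00820 = 0.0230, which is 109% of 0.021.

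CIMT, all between-patient: everyone with a 12-month scan counts fully, 117.5 and 123.4.
- SE = 0.053 × √(1/117.5 + 1/123.4) = 0.00683. Power is 69% and the detectable effect 91%.

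The same calculation for the others treats LVMi as a slope of 5 g/m2/yr with SD 47/3, and takes the upper end of power with the flow chart's 6-month visit:

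| Outcome | Enrolled per arm | Power | Detectable effect |
|---|---|---|---|
| CIMT | 155 | 54-69% | 91-109% |
| PWV | 138 | 54-75% | 86-109% |
| LVMi | 155 | 54-75% | 159-204% |

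The top of each power range treats a slope from the shortest follow-up as equal to a three-year slope. With 75% of the variance between patients, power is 59-60% for all three.

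**4. Sensitivity to the readings assumed.**
- If 0.053 came from two-year annual series, CIMT power is 74% (half of the variance visit error) to 90% (all visit error). With no visit error it stays at 69%.
- If 1.0 m/s is a per-visit error SD, PWV power with annual visits is 99.6% with no between-patient slope SD, 89% at 0.5 m/s/yr, 82% at 0.6 and 67% at 0.8.
- If all 386 per arm have LVMi, about 168 and 195 complete three years. Then SE = 47 × √(1/168 + 1/195) = 4.95, the detectable difference is 13.9 g/m2, and power for 15 is 86%.

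**The case against.** **The numbers may be evaluable patients.** Section 7.6.3.1 speaks of patients to be enrolled, whereas 7.6.3.2 does not. On that reading 80% power stands. This is fair, but the protocol then gives no enrolment target for a sub-study run in a limited number of centres, so a correction is needed either way.

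**The size of the shortfall is not fixed by the documents.** This stands. The ranges need a variance split, a source-series length and an interpretation of the PWV SD that 7.6.3.2 does not supply, and some readings in step 4 bring power above 80%.

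**The protocol already admits weak inputs.** It says CIMT and PWV data in HD patients are lacking and claims only large detectable effects (80% and 150%). That softens the consequence but does not account for the missing attrition.

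**Stronger readings the documents do not support.** A reader might infer that true power is 48%, or that LVMi can detect only a 219% effect (21.9 g/m2). Both come from three-year completers alone, whereas 7.6.2 plans a model that uses partial data for LVM too, and 7.5.4 does not confine LVMi to 155 per arm. A reader might also infer that extra carotid segments add spurious change through missing images; the protocol says nothing on this.

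**Conclusion.** The omission is established: 155, 138 and 155 per arm contain no allowance for losses that the preceding subsection assumes.

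Its size is conditional. The ranges in step 3 hold if the numbers are enrolled patients, the main trial's mortality and transplant rates apply in the sub-study, and the SDs describe full three-year slopes. For LVMi they also require that only 155 per arm are measured. Under those conditions no variance split restores 80%. Outside them the documents do not settle the figure.

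The mismatch between the CIMT definition in 7.5.5 and the common-carotid inputs in 7.6.3.2 is real, but it calls for reconciliation and does not itself show a loss of power. These are secondary outcomes, so the point is worth correcting without bearing on the primary design.

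**What to change.** In 7.6.3.2, do one of the following:

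- Restate power or detectable effect with the attrition of 7.6.3.1, showing the assumed variance split and the length of the source series.
- State that 155 and 138 are evaluable patients, define evaluable, and give the enrolled number. With mean retention (43.6% + 50.5%)/2 = 47.0% at three years, this is about 155/0.470 = 330 and 138/0.470 = 294 per arm. If a 12-month measurement suffices, mean retention is 77.7% and the numbers are about 200 and 178.

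In addition:

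- Say whether LVMi is measured in all randomised patients or in 155 per arm.
- Say whether 1.0 m/s is a repeat-measurement SD or a slope SD, and reconcile the PWV schedule: the flow chart has a 6-month visit, 7.5.5 has annual visits only.
- Reconcile the CIMT outcome in 7.5.5 with the common-carotid inputs, by changing either the definition or the inputs.

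The cost of restating is wording and less favourable stated figures, with no new measurements. Keeping 155 and 138 as evaluable numbers would mean enrolling more patients in the sub-study.

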7.6.4 Interim analysis

In this study, sequential (interim) analyses will be performed. The reason for this approach is that on average less patients are needed in the study when the expected difference in the primary outcome variable is real or when no difference can be expected anymore. Sequential analyses are performed on survival outcome variables according to the double triangular test as described by Whitehead[[117]](#endnote-118) and implemented in the computer programme PEST version 4.[[118]](#endnote-119) The sequential (interim) analyses will be performed by an independent data monitoring board (DMB).

This DMB will be initiated to evaluate the findings of the interim analyses. The DMB consists of a biostatistician (chairman), a nephrologist, an internist, a vascular surgeon and a clinical epidemiologist. The steering committee will provide the DMB every 2 months with the relevant database to perform the unblinded analyses. The main task of the DMB is to decide whether the analyses provide definite proof of either efficacy or no efficacy with respect to the primary outcome. The limits upon which these decisions are to be decided have been defined at the start of the study by the steering committee, advised by the biostatistician [name].

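### Section 7.6.4 treats a stop for no difference as possible definite proof of no efficacy, but in the named sequential test such a stop is only a failure to reject

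*Protocol*

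**What the plan says.** Section 7.6.4 of the protocol plans sequential analyses of the survival outcomes by the double triangular test. One reason given is that fewer patients are needed on average when the expected difference is real "or when no difference can be expected anymore". The section then describes the board's main task: to "decide whether the analyses provide definite proof of either efficacy or no efficacy with respect to the primary outcome". The limits for these decisions are said to have been set at the start, but they are not given.

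Section 7.6.3.1 fixes the error rates. For a 20% reduction in all-cause mortality it states that "with a two-sided alpha of 0.05 and a power of 80%, about 772 patients need to be enrolled" and followed for three years. It starts from a control rate: "the 3 year all cause mortality rate among subjects with ESRD is 44% based on RENINE data". On the sequential plan it adds: "In these patients we expect about 250 events to come to a decision". The same control rate, reduction, alpha and power are used for fatal and non-fatal cardiovascular events.

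No equivalence margin, and no rule based on a confidence interval, appears anywhere in the protocol.

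**The concern.** The sentence in 7.6.4 gives two verdicts the same strength, and the design does not. A false claim of benefit has a probability of 2.5% when there is no effect. A no-difference verdict has a probability of about 20% when the full planned benefit exists, and more when the benefit is smaller. The first can fairly be called strong evidence. The second is non-rejection at 80% power.

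This affects how an early stop is read. The protocol's Summary expects strong evidence and an effect on practice, and one primary endpoint is mortality. Section 5.4.4 declines to draw firm conclusions from an earlier small randomised study that found no effect, because it was too small. Section 7.6.4 does not apply the same caution to a non-significant stop in this trial. A moderate real benefit could be recorded as disproved.

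**Working it through.** **Inputs.** From 7.6.3.1: two-sided alpha 0.05 (0.025 for each of the two triangular tests), power 80%, control mortality 44% at three years, a 20% reduction, about 250 events to a decision. From 7.2.2: 1:1 allocation. From 7.6.4: double triangular test, data to the board every two months. The number of looks is not stated, so it was varied.

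**Planned effect.** Read as a risk reduction, 44% × 0.80 = 35.2%, so HR = ln(0.648)/ln(0.56) = 0.748 and θ = −ln(0.748) = 0.290.

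**Boundaries.** The triangular test is rescaled for 80% power:

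- θ' = 2 × 1.960 × 0.290 / (1.960 + 0.842) = 0.406
- a = (2/θ') × ln(20) = 14.77
- c = θ'/4 = 0.101
- outer lines: ±(a + cV)
- inner (no-difference) lines: ±(−a + 3cV)
- V = events/4, with a correction of 0.583 × √(increment in V) for discrete looks

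The inner region opens at V = a/(3c) = 48.5, or 194 events. The apex is at V = a/c = 145.6, or 582 events.

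**The plan's own figure.** In simulation (100,000 or more trials per setting, 12 to 100 looks) this design needs on average 253 to 266 events at HR 0.748. That agrees with the stated figure of about 250. A fixed-sample design would need 374 events by the Schoenfeld formula. The agreement supports reading the stated alpha and power as those of the sequential test.

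**How often the trial ends at the no-difference boundary.**

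| True HR | Planned effect read as HR 0.748 | Planned effect read as HR 0.80 |
|---|---|---|
| 0.748 | 20% | not run |
| 0.80 | 42% | 20% |
| 0.85 | 65% | 47% |
| 0.90 | 83% | 74% |
| 1.00 | 95% | 95% |

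The 20% entries need no simulation: 100% − 80% = 20%. The second column changes hardly at all with the number of looks. The third column belongs to a design averaging about 430 to 450 events at its planned effect, which does not match the protocol's figure.

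**What the data exclude at such a stop.** These use unadjusted 95% intervals and HR 0.748 as the planned effect.

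- True HR 0.748: about 83% of no-difference stops have an interval that still includes 0.748 (83% to 84% across runs).
- No true effect: about 41% do (40% to 43%). Most such stops therefore exclude the planned effect.
- An observed HR of exactly 1 when the inner region first opens gives exp(±1.96/√48.5) = 0.755 to 1.325, which just excludes 0.748.
- An observed HR of 0.90 at 250 events has standard error 2/√250 = 0.126 and interval 0.70 to 1.15, which includes it.

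Whether a no-difference stop excludes the planned effect therefore depends on the estimate and interval at that stop. Reaching the boundary does not settle it.

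**The case against.** The strongest reply is that a 20% miss rate at the planned effect is simply what 80% power means. A fixed-sample trial of the same target gives nearly the same profile (20%, 42%, 65%, 83%). This stands: the figures show no defect in the boundaries, the power or the sample size, and a reader who inferred one would be wrong.

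Second, the protocol never names an inner boundary and does not order the board to stop. Section 10.5 has the board make recommendations to the steering committee. Crossing the lower outer boundary (HDF worse) would also be a finding of no efficacy, and there the evidence would be strong. This too stands. The criticism is confined to a stop for no difference, which 7.6.4 foresees when it speaks of saving patients "or when no difference can be expected anymore". That phrase is an ordinary futility rationale and is unobjectionable in itself.

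Third, a reader might infer that the trial will report HDF as having no efficacy, or that the data at such a stop always remain compatible with the planned benefit. The documents support neither. No section commits the trial to such a report, section 7.6.1 promises a log-rank test adjusted for the repeated analyses, and the intervals above exclude the planned effect in some stops.

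Fourth, how an adjusted interval is computed can properly be left to the statistical analysis plan. That is accepted. The board's decision, however, is worded in the protocol itself, and limits that say when to stop do not turn a non-rejection into proof.

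**Conclusion.** The point holds as a minor one. Section 7.6.4 lets a no-difference stop count as definite proof of no efficacy, a property the design does not have. At the stated error rates that stop occurs in about 20% of trials with the full planned benefit, 42% at HR 0.80 and 65% at HR 0.85. When the planned benefit is real, about 83% of such stops leave it inside the 95% interval.

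This assumes that the stated alpha and power are those of the sequential design, which the match to about 250 events supports, and that the 20% is a reduction in three-year risk. The interval percentages also rest on an assumed number of looks and on unadjusted intervals. The basic 20% depends only on the stated power.

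The documents do not support the stronger conclusion that the stopping rule is faulty, nor that a conclusion of no relevant benefit could never be justified.

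**What to change.** In 7.6.4, reword the board's task along these lines: *to decide whether a boundary for a difference has been crossed, or the no-difference boundary has been crossed, in which case the planned 20% reduction has not been demonstrated*. Add one sentence: *a no-difference stop is reported with the hazard ratio and its confidence interval adjusted for the sequential design, and proof of no efficacy is not claimed unless that interval excludes the planned effect*. It would help to state there whether the 20% refers to risk or to hazard. The method for the adjusted interval can go in the statistical analysis plan.

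Boundaries, alpha, power and sample size do not change. The cost is a few lines of text and an adjusted interval from an analysis already planned. The downside is that a no-difference stop will support a weaker claim than the text now promises.
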